## VII. STUDY QUESTIONS AND END-POINTS OF INTEREST FOR COHORT STUDIES

### a. Key research questions

The primary research questions in the cohort studies relate to comparisons of outcome measures between arms at Year 5, and the change from baseline and follow-up, by arm. The primary research questions are:

- 1a. Do morbidity markers among cohort children at Year 5 differ by study arm?
- 1b. How do changes in morbidity markers among cohort children from baseline to follow-up differ by arm?

Interpretation of the results of these analyses needs to be done in the context of the data on prevalence and intensity in the two arms. If data are available on malaria and other factors that could affect morbidity findings, these should be evaluated as well.

Further exploratory analysis should evaluate differences in morbidity by infection intensity. For example, in any given year, is there a relationship between intensity and morbidity measurements? Is there a relationship between changes in individual's intensity over time and changes in their morbidity measures? Note that some outcomes (e.g., liver pattern C) should be assessed taking cumulative exposure into account, whereas others are more likely to be related to contemporaneous exposure.

SCORE is committed to ensuring that the link between intensity and morbidity outcomes is evaluated. However, this is beyond the scope of the core SAP.

The original statistical analysis plans for evaluating the Cohort studies is found in Appendix J.

The following outcomes are of primary interest:

- 1.a. Height and/or weight, as calculated using WHO/CDC age-standardized Z-scores for height (HAZ), weight (WAZ) and body mass index (BAZ); these are typically treated as continuous outcomes.
- 1.b. Growth stunting (HAZ < -2) or nutritional wasting (BAZ < -2) as categorical outcomes.
- 2.a. Hb levels (continuous).

- 2.b. Anemia (categorical). Based on WHO criteria, anemia is defined as Hb < 11.5 g/dL for age < 12 years, Hb < 12 for females > 12 years, Hb < 12 for males 12-15, and Hb < 13 for males > 15. Altitude-related changes in normal circulating hemoglobin levels require adjustment of anemia cutoffs for higher elevations. The cutoffs are 0.2 gm/dL higher for each age group in Tanzania and Kenya locations as they are located at 1000-1250m elevation [1]
3. Maximum oxygen uptake, VO2 max (continuous) estimated based on shuttle run scores.
4. PedsQL scores (Total score and 4 subdomains: Psychosocial, Physical, School Performance, and Emotional) as continuous variables ranging from 0 to 100.
5. Liver patterns on abdominal ultrasound (categorical or ordinal scale).

Additional questions that could be explored relate to other ultrasound measures and whether the above measurements can be combined into a health and welfare score and be analyzed in regard to treatment arm.

#### b. Analyses, tables, and figures to be reported to SCORE from Cohort study researchers

The following describes the tables and figures expected from SCORE studies, as well as approaches to analyzing the data and examples of SAS code. Descriptive statistics such as mean and variance estimates, will be calculated. Linear or generalized linear models, which adjust for clustering effects, will be used to obtain parameters of interest, such as odds ratios (for binary outcome) and group-wise differences (continuous outcome), with their confidence limits. Confidence intervals will be based on empirical variance estimates corresponding to each of the models implemented, using sandwich estimators.

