## PREFACE

This statistical analysis plan (SAP) has been developed by SCORE team members to harmonize the evaluation of outcomes data from SCORE's 'Gaining and Sustaining' schistosomiasis control studies in Cote d'Ivoire, Kenya, Mozambique, and Tanzania, and the Cohort studies of *Schistosoma*-associated morbidity in Kenya and Tanzania. It provides guidance on appropriate data sources, variable definitions, and approaches for assessing quantitative outcomes. The intent is to provide comparable analysis of country-level data for each of these SCORE studies. The data analysis plan presented below and in the Appendices is based on statistical methods that are available using SAS. Use of other statistical analysis packages is also appropriate.

This SAP covers the studies as registered, i.e., it does not cover combined studies; however, it is strongly recommended that combined analysis be conducted for the two Sm1 studies, the two Sm2 studies, and the *S. mansoni* arms that involve SBT (Arms 1-3 from Sm1 and Arms 4-6 from Sm2).

The contents of this SAP represent a minimum analysis for each study. The tables described herein should be completed and provided to SCORE before the conclusion of the study for SCORE to use in reporting to the Bill & Melinda Gates Foundation. They should be available for sharing upon appropriate request, e.g., as supplemental tables for publications. The choice of data to present in published papers is left to authors and will reflect country-specific needs and interests; however, the definitions and approaches described in this document should be used in analysis and published results should be consistent with those from the SAP analyses. In addition, investigators should review the guidelines from CONSORT (Campbell 2012) to ensure that they address all requirements for reporting randomized trials. Additional exploratory analyses beyond those described here are encouraged.

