### b. Overview of SCORE Cohort studies of infection-associated morbidities

In addition to the Gaining and Sustaining studies, Cohort studies were started in a minimum of 8 randomly selected villages participating within each of the SCORE Sh2 and Sm2 projects, in order to determine whether the intensity of village-level MDA intervention affects measures of health and well-being among school age children. The overall goal of these studies is to provide information to policy- and decision-makers about the actual impact on morbidity of alternative strategies to multi-year MDA with praziquantel in schistosomiasis-endemic areas. Because Niger did not randomize according to the study protocol, and because of poor participation and large loss to follow-up in Mozambique, only data from Kenya and Tanzania Sm2 Cohort studies are available for analysis. Thus, no longitudinal cohort study data are available for Sh, and Sh morbidity will not be considered further in this SAP.

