#### d. Study design: Cohort studies of *Schistosoma*-associated morbidity

**Overview:** The Cohort studies are sub-studies within SCORE Gaining Control studies, i.e., in communities with  $\geq 25\%$  prevalence of schistosomiasis during eligibility testing. They involve only Arms 1 and 6 of the Gaining Control studies, selected to represent the most intensive and a much less intensive intervention sequence, respectively (see below). Enrolled children were followed for five years, with evaluation occurring at Years 1 (baseline), 3 (after two MDA treatments), and 5 (after four MDA treatments).

**Cohort study design and expected sample size:** Cohort studies aimed to enroll 100 children from at least 4 communities/villages in each study arm, for a total of 800 children per study. The two Sh2 cohorts were discontinued: Mozambique because of significant loss to follow-up and Niger because of inappropriate randomization.

| Cohort Study | Year 1 | Year 2 | Year 3 | Year 4 |
|--------------|--------|--------|--------|--------|
|--------------|--------|--------|--------|--------|

[figure not shown]

Villages for inclusion in this study were meant to be a random sample of all the villages in the two study arms of interest (Arms 1 and 6); however, to facilitate the survey work investigators were allowed to select them randomly from among a restricted group of no less than 10 out of the 25 villages in each arm, chosen, for example, to exclude very remote villages.

The protocol called for selecting the 100-child cohort from the school class that starts at 7 or 8 years of age. If there were over 100 children in this class, children were to be randomly selected for participation. If this class did not include 100 children, then all of the children in that class should have been enrolled along with a random selection of children in the next older class, in order to reach the total of 100 study subjects.

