  random intercept /subject=Village_ID;
run;
```

Binary outcome code example

```
proc glimmix;
  where Study_Year=5;
  class Person_ID Village_ID Study_Arm;
  model y = Study_Arm / dist=binomial solution or;
  random intercept /subject=Village_ID;
run;
```

Ordinal outcome code example

```
proc glimmix;
  where Study_Year=5;
  class Person_ID Village_ID Study_Arm y;
  model y = Study_Arm / dist=multinomial solution;
  random intercept /subject=Village_ID;
run;
```

Note that convergence could be an issue, and sometimes setting “method=LAPLACE” in the proc line could potentially help with the convergence.

Tables 5 (multiple tables). Comparison between Arm 1 and Arm 6 of change in morbidity outcomes from Year 1-Year 5.

For each outcome, the following type of table should be developed. The results should be as indicated in the cells below.

Example: Table 5A. Comparison of changes in **anemia** rates from Year 1 to Year 5 between Arms 1 and 6.

|                      | Unadjusted                 | Adjusted                   |
|----------------------|----------------------------|----------------------------|
| Arm (1 vs. 6) | Parameter of Interest (CI) | Parameter of Interest (CI) |
| Year          | Parameter of Interest (CI) | Parameter of Interest (CI) |
| Arm*Year      | Parameter of Interest (CI) | Parameter of Interest (CI) |
| Age           | ---                        | Parameter of Interest (CI) |

|     |     |                            |
|-----|-----|----------------------------|
| Sex | --- | Parameter of Interest (CI) |
|-----|-----|----------------------------|

*General approach to analysis:* Generalized linear mixed effect models will be used to analyze the repeatedly measured outcomes from baseline to year 5. The mixed effects model was chosen to account for random effects at the village and individual levels from repeated measures.

Model setups are similar to those from the year 5 comparison (Table 7A), but with random effects from both the “Village\_ID” and “Person\_ID”. Changes from year 1 to year 5 between arms are modeled through the interaction term between “Study\_Year” and “Study\_Arm”. Models with normal, binomial, and multinomial distributional assumptions will be applied to address outcomes that are continuous, dichotomous, or categorical, respectively. SAS code examples for unadjusted models are provided below:

*Sample code:*

Linear mixed effects model code example

```
proc mixed;

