class Person_ID Village_ID Study_Arm Study_Year(ref='1');
model y=Study_Year Study_Arm Study_Arm*Study_Year/solution;
random intercept /subject=Village_ID;
random intercept /subject=Person_ID(Village_ID);
run;
```

For binary variables

```
proc glimmix;
class Person_ID Village_ID Study_Arm Study_Year(ref='1');
model y=Study_Year Study_Arm Study_Arm*Study_Year/dist=binomial solution or;
random intercept /subject=Village_ID;
random intercept /subject=Person_ID(Village_ID);
run;
```

For ordinal outcomes

```
proc glimmix;
class Person_ID Village_ID Study_Arm Study_Year(ref='1') y;
model y=Study_Year Study_Arm Study_Arm*Study_Year/dist=multinomial solution;
random intercept /subject=Village_ID;
random intercept /subject=Person_ID(Village_ID);
run;
```

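### Cohort confidence intervals rest on as few as 4 villages per arm with no small-sample correction, and the SAP text and its sample code use different variance methods

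*Combined protocol and SAP*

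**What the plan says.** Section II.d of the main SAP gives the size of each cohort: "Cohort studies aimed to enroll 100 children from at least 4 communities/villages in each study arm, for a total of 800 children per study". Section II.b gives the same floor: "Cohort studies were started in a minimum of 8 randomly selected villages participating within each of the SCORE Sh2 and Sm2 projects". Section II.b also says that "only data from Kenya and Tanzania Sm2 Cohort studies are available for analysis", and the Preface rules out pooling them within this plan: "This SAP covers the studies as registered, i.e., it does not cover combined studies". Each country's cohort result therefore rests on its own villages.

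Section VII.a sets two primary cohort questions: whether morbidity markers differ between Arms 1 and 6 at Year 5 (Tables 4), and whether their change from baseline differs (Tables 5).

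For inference, section VII.b says: "Confidence intervals will be based on empirical variance estimates corresponding to each of the models implemented, using sandwich estimators". It names neither the clustering level for the sandwich, nor a small-sample correction, nor degrees of freedom.

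The sample SAS code in the same section fits mixed models. The Year 5 code has a village random intercept. For Tables 5, "Changes from year 1 to year 5 between arms are modeled through the interaction term" between year and arm; that code has a village intercept and a child intercept ("random intercept /subject=Person_ID(Village_ID" and closing bracket). None of the code shows an empirical-variance option, a degrees-of-freedom option or a village-by-year effect.

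**The concern.** Arm is assigned to villages, so villages are the independent replicates. With 4 per arm, the arm comparison has 2×4 − 2 = 6 degrees of freedom however many children are measured. Three features of the plan bear on this.

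- An uncorrected sandwich variance is biased low when clusters are few, and normal critical values add to the shortfall.
- The text prescribes a sandwich; the code computes model-based standard errors. Following the code as shown does not deliver what the text asks for.
- In the change code, the village intercept is constant over time and cancels out of a change. Arm*Year is then judged against within-child error, although differences between villages in how they change are the relevant replication.

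At stake is the stated confidence level of both primary cohort questions, across several morbidity markers that the SAP intends for policy use.

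**Working it through.** **Inputs from the documents.** Arms: 2. Villages per arm: k = 4 as the minimum (SAP II.b and II.d); the number achieved is not given. Children per village: m = 100 as planned. Loss to follow-up is described as large but without a figure (SAP VII.c), so 50 to 100 children were used as the range.

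**The plan's own figure.** 100 × 4 × 2 = 800 children per study, which matches section II.d.

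**Assumptions.** 95% intervals; sandwich clustered by village; balanced data and a normal outcome; normal or child-level critical values where the plan names none; ICC 0.01 to 0.10. The documents give no cohort ICC or village-by-year variance.

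**Reading 1: the text governs (uncorrected sandwich, z).** The sandwich variance has expectation (k−1)/k of the true variance. So

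coverage = P(|t with 2k−2 df| < 1.96 × √((k−1)/k)), and width needed ÷ width planned = t(0.975; 2k−2) ÷ [1.96 × √((k−1)/k)].

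At k = 4: 1.96 × √0.75 = 1.697; P(|t₆| < 1.697) = 0.8595; 2.447/1.697 = 1.442. The planned interval is 1 − 1/1.442 = 31% too narrow.

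| Villages per arm | df | Coverage | Type I error | Width needed ÷ planned |
|---|---|---|---|---|
| 4 | 6 | 86.0% | 14.1% | 1.44 |
| 6 | 10 | 89.6% | 10.4% | 1.25 |
| 8 | 14 | 91.2% | 8.8% | 1.17 |
| 12 | 22 | 92.6% | 7.4% | 1.11 |

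Simulation of the Year 5 model (40,000 runs) agrees: 85.9–86.4% at k = 4 over the ICC range. The same figure applies to the change model: about 86% whatever the village-by-year variance, because a village-clustered sandwich picks that variance up. Using 6 df without correcting the bias gives 92.2%; both corrections together give about 95%.

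**Reading 2a: the code governs, Year 5 (model-based SE, z).** With an unbiased village-level SE and z, P(|t₆| < 1.96) = 0.902. Simulation at k = 4 gives 90.3–93.8% for ICC 0.10 down to 0.01 and 50 or 100 children. Since 1.96/2.447 = 0.80, the interval is at most 20% too narrow (equivalently, the correct one is up to 25% wider). At k = 8 coverage is 92.9–93.9%.

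**Reading 2b: the code governs, change model.** Let v be the village-by-year variance as a share of total variance, and let the within-child residual be 0.5 of total (assumed). Per arm, the variance of a mean change is proportional to 0.5 + m·v. The fitted residual is only about 0.5 + 0.75·v: with Years 1, 3 and 5, m = 100 and k = 4, the village-by-year term has 12 of 1,596 residual df, and 100 × 12/1,596 = 0.75. So

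type I error ≈ P(|Z| > 1.96/r), with r = √[(0.5 + m·v)/(0.5 + 0.75·v)].

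| v | r (m = 100) | Type I error, m = 100 | Type I error, m = 60 |
|---|---|---|---|
| 0 | 1.00 | 5% | 5% |
| 0.5% | 1.41 | 16% | 12% |
| 1% | 1.72 | 25% | 18% |
| 2% | 2.20 | 37% | 28% |

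As an independent check, simulation with variance expressed as a share of within-child variance gives 74.3% coverage at 2%, which is v = 1% here and agrees with 25% error. More villages hardly help: at 5% of within-child variance, with 100 children, coverage is 57.3% with 4 per arm and 57.9% with 8.

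**The case against.** **The errors do not accumulate.** A reader might infer that sandwich bias, missing degrees of freedom and the missing village-by-year effect pile up in one analysis and make every cohort interval far too narrow. The documents do not support that. If the text governs, the omitted variance is absorbed and only the small-sample shortfall remains. If the code governs, the sandwich figure does not apply. This objection stands.

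**The change-model figures rest on an unstated variance.** With zero village-by-year variance the code's coverage is about 95%. This also stands. Non-zero values are plausible, since component 10 of the harmonized protocol expects weather, water supply and other programmes to change during the study, but that gives no size.

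**Four per arm is a floor.** It is, although the total of 800 implies exactly 4. With more villages the shortfall shrinks but is still visible at 12 per arm.

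**The code is illustrative.** The SAP calls it an example and allows other packages, so a missing option does not prove it would be left out. But the sandwich sentence is a general rule, and it names no correction either. The contents of Appendices B, J and K are not in the text available to this review, so the absence of a correction is established only for the SAP body.

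**This is a sub-study.** The point does not touch the main comparisons, which plan 25 villages per arm.

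**Conclusion.** The point holds in this form. At the planned minimum of 4 villages per arm, the stated method yields nominal 95% intervals that cover about 86%; they are 31% too narrow, for both the Year 5 and the change comparison. That figure does not depend on the ICC or on village-by-year variance; it does depend on the number of villages and on clustering by village.

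If the sample code is followed instead, the Year 5 shortfall is modest (90–94% coverage), and the change comparison ranges from no shortfall to a severe one according to a variance that the documents do not give. A claim that false-positive rates are well above 5% for both questions under every reading would go beyond the documents. What is certain is that text and code disagree, that the change code has no village-by-year effect, and that no degrees-of-freedom rule is stated.

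**What to change.** 1. State one variance method for Tables 4 and 5, name the village as the cluster, and make the code match.
2. Use village-level degrees of freedom (2k−2, with k the villages actually analysed per arm) with a bias-corrected village-clustered sandwich; or use model-based standard errors with Kenward-Roger degrees of freedom, and between-within degrees of freedom for binary and ordinal outcomes. For Arm*Year in the binary and ordinal models, set 2k−2 explicitly, because a between-within rule may class an effect that varies over years inside a village as within-village.
3. If standard errors are model-based, add a random village-by-year effect to Tables 5, for example a random intercept with subject Village_ID*Study_Year. This is not needed for valid standard errors if the corrected village-clustered sandwich is chosen.
4. Report, as a check, a t-test on village means at Year 5 and on village mean changes, each with 2k−2 df. This also serves as the fallback if the extra random effect does not converge.
5. Report the number of cohort villages analysed per arm in each country.

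The cost is SAP wording and code options; no new data are needed. Intervals will be wider: at 4 per arm, 1.44 times the uncorrected sandwich interval. The added random effect may aggravate the convergence difficulty that the SAP already notes for its mixed models, mainly for binary and ordinal outcomes.

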Table 2. Year 1/Year 5 Comparison of Prevalence and Intensity, by Arm

|                                                                   | Year 1/Year 5 Comparison |       |                         |       |                            |       |
|-------------------------------------------------------------------|--------------------------|-------|-------------------------|-------|----------------------------|-------|
|                                                                   | Prevalence               |       | Village-level intensity |       | Individual-level intensity |       |
|                                                                   | Arm 1                    | Arm 6 | Arm 1                   | Arm 6 | Arm 1                      | Arm 6 |
| Absolute difference between Year 5 and baseline            |                          |       |                         |       |                            |       |
| Relative difference between Year 5 and baseline (% change) |                          |       |                         |       |                            |       |
| Egg reduction rate (1-Year 5 intensity/baseline)           |                          |       |                         |       |                            |       |

Figure 1. Study flow by arm. (See instructions for Figure 2 in the description of tables and figures for cross-sectional analysis.)

Table 3. Descriptive results on morbidity markers, by arm, by year.

|                                      | Arm 1 (cccc) |        |        | Arm 6 (shsh) |        |        |
|--------------------------------------|--------------|--------|--------|--------------|--------|--------|
|                                      | Year 1       | Year 3 | Year 5 | Year 1       | Year 3 | Year 5 |
| Height: average Z score (SD)  |              |        |        |              |        |        |
| Weight: average Z score (SD)  |              |        |        |              |        |        |
| BMI: average Z score (SD)     |              |        |        |              |        |        |
| Prevalence of stunting % (CI) |              |        |        |              |        |        |
| Prevalence of wasting %       |              |        |        |              |        |        |

|                               |  |  |  |  |  |  |
|-------------------------------|--|--|--|--|--|--|
| (CI)                          |  |  |  |  |  |  |
| Mean hemoglobin in gm/dL (SD) |  |  |  |  |  |  |
| Prevalence of anemia % (CI)   |  |  |  |  |  |  |
| Mean Vo2 max score (SD)       |  |  |  |  |  |  |
| Mean PedsQL score (SD)        |  |  |  |  |  |  |
| Total Score                   |  |  |  |  |  |  |
| Physical                      |  |  |  |  |  |  |
| Emotional                     |  |  |  |  |  |  |
| Social                        |  |  |  |  |  |  |
| School                        |  |  |  |  |  |  |
| Liver pattern                 |  |  |  |  |  |  |
| B % (CI)                      |  |  |  |  |  |  |
| C or higher % (CI)            |  |  |  |  |  |  |

Tables 4 (multiple tables). Comparison between Arm 1 and Arm 6 of Year 5 morbidity outcomes.

For each outcome, the following type of table should be developed. The results should be as indicated in the cells below.

Example: Table 4A. Unadjusted and adjusted models for **anemia** at Year 5.

|                     | Unadjusted                   | Adjusted                   |
|---------------------|------------------------------|----------------------------|
| Arm (1 vs 6) | Parameter of Interest** (CI) | Parameter of Interest (CI) |
| Age          | ---                          | Parameter of Interest (CI) |
| Sex          | ---                          | Parameter of Interest (CI) |

*General approach to analysis:* For binary outcomes such as anemia status, the parameter of interest is typically the measure of association, such as odds ratio or relative risk. For models with other types of outcome, the parameter is the beta coefficient estimator from the corresponding models.

Generalized linear mixed effects models will be used to analyze the year 5 outcome. A generalized linear mixed effects model was chosen to account for random effects at the village level in year 5 comparison. The unadjusted model is a between-arm comparison without adjustment for other covariates. The adjusted model proposed here only includes adjustment for age and sex.

Generalized mixed effects models with normal, binomial, and multinomial distributional assumptions will be applied to address outcomes that are continuous, dichotomous, or categorical, respectively. SAS code examples for unadjusted models are provided below:

Sample code:

Linear mixed effects model code example

```
proc mixed;
  where Study_Year=5;
  class Person_ID Village_ID Study_Arm;
  model y = Study_Arm / solution;
  random intercept /subject=Village_ID;
run;
```

Binary outcome code example

```
proc glimmix;
  where Study_Year=5;
  class Person_ID Village_ID Study_Arm;
  model y = Study_Arm / dist=binomial solution or;
  random intercept /subject=Village_ID;
run;
```

Ordinal outcome code example

```
proc glimmix;
  where Study_Year=5;
  class Person_ID Village_ID Study_Arm y;
  model y = Study_Arm / dist=multinomial solution;
  random intercept /subject=Village_ID;
run;
```

Note that convergence could be an issue, and sometimes setting “method=LAPLACE” in the proc line could potentially help with the convergence.

Tables 5 (multiple tables). Comparison between Arm 1 and Arm 6 of change in morbidity outcomes from Year 1-Year 5.

For each outcome, the following type of table should be developed. The results should be as indicated in the cells below.

Example: Table 5A. Comparison of changes in **anemia** rates from Year 1 to Year 5 between Arms 1 and 6.

|                      | Unadjusted                 | Adjusted                   |
|----------------------|----------------------------|----------------------------|
| Arm (1 vs. 6) | Parameter of Interest (CI) | Parameter of Interest (CI) |
| Year          | Parameter of Interest (CI) | Parameter of Interest (CI) |
| Arm*Year      | Parameter of Interest (CI) | Parameter of Interest (CI) |
| Age           | ---                        | Parameter of Interest (CI) |

|     |     |                            |
|-----|-----|----------------------------|
| Sex | --- | Parameter of Interest (CI) |
|-----|-----|----------------------------|

*General approach to analysis:* Generalized linear mixed effect models will be used to analyze the repeatedly measured outcomes from baseline to year 5. The mixed effects model was chosen to account for random effects at the village and individual levels from repeated measures.

Model setups are similar to those from the year 5 comparison (Table 7A), but with random effects from both the “Village\_ID” and “Person\_ID”. Changes from year 1 to year 5 between arms are modeled through the interaction term between “Study\_Year” and “Study\_Arm”. Models with normal, binomial, and multinomial distributional assumptions will be applied to address outcomes that are continuous, dichotomous, or categorical, respectively. SAS code examples for unadjusted models are provided below:

*Sample code:*

Linear mixed effects model code example

```
proc mixed;
class Person_ID Village_ID Study_Arm Study_Year(ref='1');
model y=Study_Year Study_Arm Study_Arm*Study_Year/solution;
random intercept /subject=Village_ID;
random intercept /subject=Person_ID(Village_ID);
run;
```

For binary variables

```
proc glimmix;
class Person_ID Village_ID Study_Arm Study_Year(ref='1');
model y=Study_Year Study_Arm Study_Arm*Study_Year/dist=binomial solution or;
random intercept /subject=Village_ID;
random intercept /subject=Person_ID(Village_ID);
run;
```

For ordinal outcomes

```
proc glimmix;
class Person_ID Village_ID Study_Arm Study_Year(ref='1') y;
model y=Study_Year Study_Arm Study_Arm*Study_Year/dist=multinomial solution;
random intercept /subject=Village_ID;
random intercept /subject=Person_ID(Village_ID);
run;
```

